The combination of bortezomib and carboplatin was also tested in 22 patients with platinum- and taxane-resistant ovarian cancer [36]. In these heavily pretreated patients no objective response was seen, but 44% (8 of 18 evaluable patients) had a stable disease. Based on these data, this drug combination could show efficacy in triple-negative breast cancers, known to be biologically similar to ovarian cancer.

The bortezomib and carboplatin regimen was combined with gemcitabine in a triple drug first line regimen in a phase II trial in patients with advanced non-small cell lung cancer (*n* = 114) [37] and in the same indication in combination with bevacizumab within a phase I/II trial (*n* = 16) [38]. The leading grade 3 and 4 toxicities occurring in more than 15% of patients were thrombocytopenia (63%) and neutropenia (52%) in combination with gemcitabine, and thrombocytopenia (58%), lymphocytopenia (25%), diarrhea (25%), nausea (19%), and vomiting (19%) in combination with bevacizumab. Response rates were 23% in the gemcitabine containing trial and 44% in the bevacizumab containing trial [37, 38].

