## Methods

### Study design

The phase I part of this study uses an alternate dose escalation accelerated titration design [39] as outlined in Fig. 1 and Table 1. In the accelerated dose-escalation phase a single-patient cohort per dose level will be enrolled, until one dose limiting toxicity (DLT) or 3 moderate toxicities, as outlined below, are observed during cycle 1, or until dose level 4 is reached. At this dose level the cohort is expanded to three patients and dose escalation reverts to a conventional 3 + 3 escalation design [40]. Dose limiting toxicities (DLTs) are defined as drug related adverse events preventing the administration of the drug combination. Such toxicities are defined as grade 3 or 4 non-hematologic toxicities (excluding alopecia, nausea, emesis, diarrhea), grade 3 or greater nausea and/or emesis despite the use of optimal anti-emetic prophylaxis, grade 3 or greater diarrhea that occurs despite maximal supportive therapy, grade 2 peripheral neuropathy with pain or polyneuropathy greater or equal grade 3, neutropenia grade 4 for more than 7 days, febrile neutropenia grade 3, thrombocytopenia grade 4, or thrombocytopenia grade 3 with bleeding. Moderate toxicities are defined as any grade 2 non-hematologic toxicity excluding alopecia, or any grade 3 hematologic toxicity.

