**Fig. 1 Fig1:**
[figure not shown]
Accelerated titration design of the phase I part of the trial. Illustration of the accelerated titration design of the phase I part of the trial. Each box outlined in bold represents a cohort containing the indicated number of patients treated at a given dose level. Ixazomib will be administrated orally on days 1, 8, and 15 and carboplatin intravenously on days 1, 8, and 15 of a 4-week cycle. Drug dosages per dose level are given on the left side of the graph. DLT = dose-limiting toxicity; AUC = area under the curve

**Table 1 Tab1:** Drug dosages per dose level

Dose level	Ixazomib orally on days 1, 8, 15 every 4 weeks	Carboplatin i.v. on days 1,8 and 15 every 4 weeks
1	3 mg	AUC 1.5
2	3 mg	AUC 2
3	4 mg	AUC 2
4	4 mg	AUC 2.5

AUC = area under the curve

The maximum-administered dose (MAD) is defined as the dose at which DLT or 3 moderate toxicities occur in at least two of six patients treated at that dose level. The dose-level just below the MAD is considered the maximum-tolerated dose (MTD), providing that DLT or 3 moderate toxicities are observed in fewer than two of six treated patients (or fewer than one third if more than six patients will be treated) at that dose level. Determination of MAD and MTD is based on DLT or 3 moderate toxicities observed during the first treatment cycle.

Beginning with the 2nd cycle an intra-patient dose escalation is allowed. This is separate from the alternate dose escalation design of the phase I part. If the nadir ANC was ≥500/mL, the nadir platelet count ≥50,000/mL, and non-hematologic toxicities were grade ≤ 1 in the previous cycle, the current dose level can be escalated by one dose level by each cycle. After completion of phase I, all patients, that are treated with a dose below the determined MTD, can be dose escalated at the discretion of the investigator [39, 41].

After establishing MTD in phase I, accrual continues in phase II to evaluate the efficacy and safety of the combination therapy. A total of 41 evaluable patients will be included (patients enrolled in the phase I part within the conventional dose escalation phase at the dose level considered as the MTD may be included).

All subjects will continue on study drugs until disease progression, unacceptable toxicity or treatment discontinuation for any other reason, respectively.

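### At dose levels 1–3 the intra-patient escalation rule does not exclude a patient whose own cycle 1 counted toward the MAD through three grade 3 hematologic toxicities (minor, optional)

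*Protocol article*

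**What the plan says.** All the rules are in the Protocol article, Methods, Study design.

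- **Moderate toxicity.** "Moderate toxicities are defined as any grade 2 non-hematologic toxicity excluding alopecia, or any grade 3 hematologic toxicity".
- **Event against a dose level.** "The maximum-administered dose (MAD) is defined as the dose at which DLT or 3 moderate toxicities occur in at least two of six patients". The count is made separately for each level. A patient with three moderate toxicities therefore weighs the same as a patient with a DLT. The window is cycle 1: "Determination of MAD and MTD is based on DLT or 3 moderate toxicities observed during the first treatment cycle".
- **Intra-patient escalation.** It is open from cycle 2. The hematologic tests are "If the nadir ANC was ≥500/mL, the nadir platelet count ≥50,000/mL". The rule then continues "and non-hematologic toxicities were grade ≤ 1 in the previous cycle, the current dose level can be escalated by one dose level by each cycle".
- **Relation between the two.** "This is separate from the alternate dose escalation design of the phase I part".
- **Levels.** Table 1 has four, so a step up exists only from levels 1, 2 and 3.

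The Discussion repeats that escalation requires toxicities in a predefined range, but adds no criterion.

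**The concern.** The escalation rule is printed as a complete if-then statement with numeric limits. It does not refer to DLT, to the count of moderate toxicities, or to hemoglobin, leukocytes or lymphocytes. The cohort rule does count grade 3 toxicities in those lineages. A patient can thus be recorded as evidence against her current dose and, in the next cycle, qualify for a higher one.

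What is at stake is the safety of that individual patient. The Background section on carboplatin names increased hematotoxicity as the drug's drawback against cisplatin, and blood counts are where the gap lies. During accelerated titration the effect is odd: one such patient at level 1 stops the single-patient cohorts and holds the trial at level 1 for more safety data, while she herself meets the printed conditions for level 2.

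**Working it through.** **The plan's own figure.** The only number attached to this event is in Determination of sample size: power above 87% to see at least one of three patients with the event when its probability is 50%. 1 − 0.5³ = 0.875, which agrees. The point does not depend on it.

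**Which patients can slip through.** Three moderate toxicities that include a grade 2 non-hematologic one fail the grade ≤ 1 test. Only three hematologic toxicities can pass. Taking neutropenia, thrombocytopenia, anemia, leukopenia and lymphopenia as the candidates gives 10 possible triples.

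| Reading of the floors | Triples that pass |
|---|---|
| Every grade 3 neutropenia and thrombocytopenia assumed blocked | 1 of 10: anemia, leukopenia, lymphopenia |
| Per microlitre, assuming grade 3 means ANC 500 to <1000 and platelets 25,000 to <50,000 | 4 of 10: any three of neutropenia, anemia, leukopenia, lymphopenia |
| Per mL, as printed | 10 of 10 |

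The article does not print the grade limits, so the second row is an assumption; the first row needs none. At least one triple passes on every reading.

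**Size, as illustration only.** Rates come from the Background section on combining ixazomib and carboplatin. They are for bortezomib plus carboplatin with a third drug in lung cancer, grades 3 and 4 together, and are not stated to be cycle 1. Independence is assumed throughout.

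*Bevacizumab trial (n = 16).* Lymphopenia L = 0.25. Neutropenia N, anemia A and leukopenia W are not listed among toxicities above 15%, so each is set at 0.15. Patients below the platelet floor (58%) or with grade 3/4 diarrhea (25%) are removed: (1 − 0.58) × (1 − 0.25) = 0.315.

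- Named three (A, W, L): 0.25 × 0.15² = 0.005625; × 0.315 = 0.00177, or 0.18%.
- Any three or more of N, A, W, L: 3 × 0.25 × 0.15² × 0.85 + 0.15³ × 0.75 + 0.25 × 0.15³ = 0.01434 + 0.00253 + 0.00084 = 0.01772 (from unrounded terms); × 0.315 = 0.00558, or 0.56%.
- With the unlisted lineages at 0.05 instead: 0.02% and 0.06%.

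*Gemcitabine trial.* "The leading grade 3 and 4 toxicities occurring in more than 15% of patients were thrombocytopenia (63%) and neutropenia (52%) in combination with gemcitabine". With N = 0.52, the other three lineages at 0.15 and factor 1 − 0.63 = 0.37: 0.15³ × 0.37 = 0.00125, or 0.12%, for the named three; 0.03321 × 0.37 = 0.01229, or 1.2%, for any three of four. The 52% includes grade 4 neutropenia that the ANC floor would block.

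*Across patients (bevacizumab figures), 1 − (1 − p)ⁿ.* For the three single patients planned at levels 1–3: 0.5% or 1.7%. For the extreme of six at each of those levels (n = 18): 3.1% or 9.6%.

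**How much independence matters.** Keep the bevacizumab lineage and platelet rates, leave out the diarrhea factor and let the correlation vary freely. The named three can then occur in anything from 0 to 0.15 of patients, the smallest single rate. For any three of four, let x be the share with L plus two others and y the share with N, A and W. Then 2x + 3y ≤ 0.45, so the maximum is 0.225 and the minimum 0. The data cannot place the truth within these ranges.

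**The case against.** The strongest case against is that this is a preference and not a defect. The article declares the two rules separate: one defines a cohort's MAD, the other an individual's optional next dose. Dose modification after toxicity is commonly left to the full protocol, which is not shown and may already contain the restriction. The individual rule is also stricter in places. A single grade 2 non-hematologic toxicity blocks it. Read per microlitre with the usual grade limits, so does one uncomplicated grade 3 thrombocytopenia or a brief grade 4 neutropenia, neither of which alone is a MAD event.

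Most of this stands as to weight:

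- The rules overlap, and neither is uniformly looser. A reader might infer a contradiction between them, but nothing printed, including the Discussion, shows that the two ranges were meant to match.
- Escalation is permissive, and the investigator may decline.
- Once thrombocytopenia is blocked, every passing triple needs at least two white-cell abnormalities counted separately. The word covering any grade 3 hematologic toxicity supports that; if they count once, the case disappears.
- The illustrative rates omit other blocking toxicities (nausea and vomiting, 19% each, and all grade 2 non-hematologic events), so on that count they run high.

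It does not remove the point. The rule is not merely abbreviated: it is printed with its limits and, followed exactly, admits this patient. Separation explains why MAD and MTD are untouched, but gives no reason to raise the dose for someone just counted against the lower one.

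**Conclusion.** The point holds as a minor, optional patient-safety improvement. At levels 1–3 the printed rule does not exclude a patient whose cycle 1 counted toward the MAD through three grade 3 hematologic toxicities outside the ANC and platelet floors. This rests on counting moderate toxicities per patient, as the MAD sentence does, and on counting leukopenia and lymphopenia separately. It cannot arise at level 4.

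The case is probably rare. The 0.02% to 1.2% per patient is an illustration under independence and not an estimate.

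Three stronger readings are not supported:

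- A reader might infer that MAD or MTD is distorted. Both rest on cycle 1, and escalation starts in cycle 2. Nor is the phase II response test affected.
- A reader might take 15% or 22.5% as the likely frequency. Those are the upper ends of ranges that start at zero.
- A reader might infer that the rule plainly lets a DLT through, since the DLT list includes "febrile neutropenia grade 3, thrombocytopenia grade 4, or thrombocytopenia grade 3 with bleeding" and the escalation rule does not name febrile neutropenia. Whether the ANC floor catches it depends on a cut-off the article does not print, so the point does not rest on it.

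**What to change.** Add one condition to the intra-patient escalation rule in Study design: a patient who had a DLT or three moderate toxicities in the previous cycle is not eligible for intra-patient escalation. Naming DLT as well settles febrile neutropenia without argument over cut-offs. If the full protocol already has this restriction, confirming that is enough.

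The cost is one sentence, using toxicity data already collected each cycle. The downside is that a few patients lose the option of a higher dose.

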## Discussion

Inhibition of DNA repair mechanisms by proteasome inhibitors could sensitize triple-negative breast tumors to DNA damaging agents like platinum salts. Within the AGMT MBC-10 trial we utilize an innovative straight forward trial concept supporting an expedite early development for the drug combination of ixazomib and carboplatin for the treatment of TNBC. For both, carboplatin and ixazomib, the single agent maximum tolerable dose (MTD) is already known. In order to reduce the number of patients treated at sub-effective doses we use an accelerated titration design in which a single patient will be enrolled per dose level [39]. If toxicities during cycle 1 are outside the predefined acceptable range, or dose level 4 have been reached, the cohort is expanded to three patients and dose escalation reverts to a conventional 3 + 3 design. During the phase I part of the trial, an intra-patient dose escalation will provide the individual patient with a higher chance to reach effective drug dosages. Such escalation is allowed beginning with cycle 2 if toxicities in the previous cycles were within a predefined range [39, 41]. After determining the MTD, patient enrollment will seamless continue into the phase II part of the trial without any delay due to regulatory issues. This trial is accompanied by a translational research program, aimed to identify a subgroup of patients benefiting most within this heterogeneous disease and to decipher resistance mechanisms to this novel drug combination.

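### In phase I, intra-patient escalation depends only on the patient's own previous cycle, so as written she can move ahead of the cohorts, above a level held for toxicity, or briefly onto the MAD

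*Protocol article*

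**What the plan says.** All of this stands in the protocol article.

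- **Cohort rule** (Methods, Study design). One patient is entered per level until one DLT or 3 moderate toxicities "are observed during cycle 1, or until dose level 4 is reached". Then: "At this dose level the cohort is expanded to three patients and dose escalation reverts to a conventional" 3 + 3 scheme.
- **Intra-patient rule** (same section, after Table 1). From cycle 2 a patient may go up if her nadir neutrophil and platelet counts and her non-hematologic toxicity (grade 1 at most) in the previous cycle are within limits. The step is one level: "the current dose level can be escalated by one dose level by each cycle".
- **Relation between the two** (same place). "This is separate from the alternate dose escalation design of the phase I part".
- **The MTD as a reference dose** (same place). It appears only for the later period: "After completion of phase I, all patients, that are treated with a dose below the determined MTD, can be dose escalated", at the investigator's discretion.
- **What counts towards the MTD** (same place). "Determination of MAD and MTD is based on DLT or 3 moderate toxicities observed during the first treatment cycle".
- **Restatement** (Discussion). "Such escalation is allowed beginning with cycle 2 if toxicities in the previous cycles were within a predefined range". No cohort condition is added.

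**The concern.** A cohort design limits how many patients receive a dose before there is evidence that it is tolerated, and it stops escalation when toxicity appears. Every term of the intra-patient gate concerns the patient herself. None asks whether her next level has been opened to a cohort, whether the level below it is being expanded because of toxicity, or whether it has already been found to be the MAD. A patient who tolerates level k well shows her own tolerance at k, not the safety of level k + 1.

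At stake is the safety of a few phase I patients. The case that matters most is a toxicity signal that halts the cohorts but, on the text, does not halt a patient already on treatment. Any event she then has falls in cycle 2 or later. It is reported in the safety analysis but does not enter the MAD/MTD decision.

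**Working it through.** The article gives no figure for this rule. Its one phase I operating figure (Determination of sample size, greater than 87%) reproduces as 1 − 0.5³ = 0.875 and is not affected. What follows is a timeline.

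**Inputs.** From the article: 28-day cycles, four levels, one patient per level at first, intra-patient moves from cycle 2, one level per cycle. Assumed: a level opens once the cohort below has completed cycle 1 without a stopping event; patient 1 starts level 1 on day 1 and meets her own gate every cycle.

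Patient 1 may start level L on day 1 + 28(L − 1): **days 29, 57 and 85** for levels 2, 3 and 4.

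**1. No toxicity, no enrolment gaps.** Cohorts start on the same days, 29, 57 and 85, and complete cycle 1 on days 56, 84 and 112. Her lead over the first cohort patient is 0 days. She starts 28 days before the level could be cleared, but it has been opened.

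**2. No toxicity, assumed gap of 14 days before each new cohort.** The first cohort patient at level L starts on day 42(L − 1) + 1.

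| Level | Patient 1 | Level opens | First cohort patient | Ahead of opening | Ahead of cohort patient |
|---|---|---|---|---|---|
| 2 | 29 | 29 | 43 | 0 | 14 |
| 3 | 57 | 71 | 85 | 14 | 28 |
| 4 | 85 | 113 | 127 | 28 | 42 |

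**3. DLT in the first level 2 cohort patient (assumed), no gaps.** She starts on day 29, so the DLT falls on some day d from 29 to 56. Level 2 expands from 1 to 3 on day d + 1 and from 3 to 6 on day d + 29. If no second patient has a stopping event, level 3 opens on day d + 57 and level 4 on day d + 85.

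| | d = 29 | d = 56 | Patient 1 may start | Her lead |
|---|---|---|---|---|
| Level 3 opens | 86 | 113 | 57 | 29 to 56 days |
| Level 4 opens | 114 | 141 | 85 | 29 to 56 days |

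If a second level 2 patient does have an event, level 2 is the MAD and level 3 never opens. Patient 1 may by then already be on level 3, above the MAD.

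**4. Move onto a declared MAD.** Once a level is found to be the MAD, phase I continues until six patients have been treated at the level below. With n already treated there, 6 − n are needed: none if n = 6 (window 0 days); three if n = 3 (about 28 days); five if n = 1 (about 28 days in one group, 56 in two). Only in that window can a patient at the level below step onto the MAD under the phase I rule.

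**The case against.** The strongest reply is that this is silence in a condensed article. The wording is permissive, the full protocol and the diagram in Fig. 1 are not shown, and a cap may stand there. Calling the rule separate may mean only that later cycles do not feed cohort decisions. The choice is also deliberate: the Discussion says that "an intra-patient dose escalation will provide the individual patient with a higher chance to reach effective drug dosages". There are safeguards too: one level per cycle, level 4 as the top, known single-agent MTDs, and a non-hematologic limit stricter than the cohort stopping rule.

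Part of this stands. A full protocol could hold a cap, and the safeguards are real. But the article does more than stay silent: it gives numeric conditions, step size, start and relation to the cohorts, and someone who follows it exactly may make the moves shown above. Reading "separate" narrowly supplies no cohort condition either. Single-agent MTDs do not establish that the combination is tolerated, which is the question phase I asks.

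Stronger readings are tempting, but the documents do not support them:

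- **That patients will routinely flood uncleared levels.** If every patient stays on treatment and passes every gate, the numbers dosed before clearance are 1 + 1 = 2, 1 + 2 = 3 and 3 + 3 = 6 at levels 2, 3 and 4, against 1, 1 and 3 from cohorts alone. This is a ceiling. Patient 1 would have to pass three gates in a row in pretreated metastatic disease, and none of the three counts exceeds the six patients on which the MAD decision rests.
- **That entering a level before its cohort completes cycle 1 is in itself an error.** Without toxicity or gaps she enters an opened level alongside its first cohort patient. Waiting for full clearance there trades safety against the stated aim of reaching effective doses.
- **That patients may exceed the MTD after phase I.** Escalation is then limited to patients below the MTD, and with the one-level step a move reaches the MTD at most.
- **That the MTD or phase II is distorted.** The MAD and MTD use first-cycle events only, and nothing in this rule enters the two-stage response design.

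**Conclusion.** The point holds as a gap in phase I patient safety. As written, a patient may move to a level not yet opened to a cohort, to a level above one where cohorts are held after a DLT or 3 moderate toxicities, or, for between 0 and about 56 days, onto a level already found to be the MAD.

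Its size depends on events. It is largest after a toxicity signal: a lead of 29 to 56 days at levels 3 and 4, assuming one DLT at level 2, expansion 1 to 3 to 6, no gaps, and a patient 1 who stays within her limits. With slow enrolment it is moderate, and with neither toxicity nor gaps it is small. No probability can be attached, because the article gives no toxicity rates for this combination. It is worth correcting because the remedy is inexpensive.

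**What to change.** Add to the intra-patient paragraph after Table 1: during phase I, a patient may be escalated only to a level already opened to cohorts and not under hold or expansion for toxicity; never above a level that is being expanded because of toxicity; and never to a level declared the MAD. Preferably, the target level's cohort should also have completed cycle 1 without a stopping event. If the full protocol already says this, the article should state it. The limit after phase I and the first-cycle definition of MAD and MTD need no change.

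**Cost.** No new data and no change in sample size, but because the trial has been enrolling since November 2016, a dosing rule would change in a running study. Some patients escalate later or not at all, which works somewhat against the aim of reaching effective doses:

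- *Minimum form.* No delay without toxicity and gaps. With the 14-day gap, patient 1's next cycle starts after levels 3 and 4 open are days 85 and 113, 28 days later than now. In the DLT example they are days 113 and 141, 56 days later.
- *Preferred form.* Even in the fastest case she reaches levels 2, 3 and 4 on days 57, 85 and 113 instead of 29, 57 and 85, one cycle later each time, and later still with enrolment gaps.
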